### Tertiary outcome measures

The patients’ level of satisfaction regarding the procedure and overall experience will be reported verbally to nursing and recorded on the questionnaire based on a 5-point Likert scale where a minimum score of 1 = very dissatisfied whereas a maximum score of 5 = very satisfied. In addition, their willingness to undergo a similar surgery using the same anesthetic technique will be documented as “yes” or “no” and proportions will be compared for the two groups.

### Independent variables

Information will be captured on baseline characteristics such as sex, age, comorbidities, and ASA classification.

*Participant timeline* (see Table 1).

**Table 1 Tab1:** SPIRIT timeline

	**Enrolment**	**Time of intervention**	**Post-allocation**			
**Timepoint**^******^	***1 week***	**0 h**	**6 h**	**12 h**	**24 h**	**30 days**
Enrolment						
Eligibility screen	X					
Informed consent	X					
Allocation	x	X				
Interventions						
Euthyroidectomy under LA or GA		**X**				
Assessments						
Socio-demographics, ASA class	X	X				
Early post operative complications			x	X	x	X
Cost implications of treatment			x	x	x	x
Patients’ level of satisfaction						X

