### Primary outcome measures

The primary outcome measures will be early 30-day post-operative complications (harms), including: pain, nausea, vomiting, hematoma, transient voice changes, and surgical site infection rates.

The complications will be reported verbally to nursing or to attending physicians for evaluation and recorded on a questionnaire in accordance with MedDRA® version 4.21 standardized reporting on medical and surgical procedures. The post-operative pain will be measured based on visual analogue scale of 0–10 where 0 means no pain and 10 means the worst possible pain. The pain will be assessed at an interval of 6, 12, and 24 h and at 30 days. The mean pain scores will be compared at using Student’s *t*-test, assuming normal distribution; otherwise, medians will be compared using non-parametric Kruskal–Wallis rank sum test.

The nausea and vomiting will be reported to nursing or attending physicians and recorded to the questionnaire using a nausea score on a scale of 0–9 where 0 means no symptom and 9 means very severe. The symptoms will be assessed at an interval of 6, 12, and 24 h and at 30 days. The mean nausea scores will be compared using a paired Student’s *t*-test, assuming normal distribution; otherwise, medians will be compared using non-parametric Kruskal–Wallis rank sum test.

Complications: hematoma, transient voice changes, and surgical site infection rates will be assessed at 6, 12, and 24 h and at 30 days will be reported in accordance with the Clavien Dindo classification of surgical complications [27], where grade I represents complications that do not require any additional intervention, grade II requires pharmacological treatment but not radiological or surgical intervention for instance blood transfusion, grade III requires radiological or surgical re-intervention, e.g., neck exploration and hematoma evacuation, grade IV representing life-threatening complications with at least one organ dysfunction such as respiratory failure that requires intensive care admission. The difference in proportions will be compared using Wilcoxon sum rank test.

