### Randomization, blinding and allocation concealment and implementation

Patients who meet the inclusion criteria will be assigned randomly by research assistants to either local anesthesia group (L) or general anesthesia group (G) using envelope concealment. Half of these concealed envelopes will contain letter L and the other half letter G to represent LA and GA, respectively. Permuted balanced block randomization will be performed by the study supervisor to derive a random sequence of numbers that will represent the two arms in an allocation ratio of 1:1. The random sequence numbers will be generated using a web-based software (https://www.random.org/). A set of 52 numbers will be generated beginning with a minimum of 1 and maximum of 52. The numbers will then be used to label the sealed envelopes sequentially and will be concealed to research assistants. The content of the envelope will be concealed only to be opened in the operating room for the anesthesia providers to know what anesthetic technique is to be used for the research participant.

The study participants at this point in the operating room will not be blinded as the research and ethics committee considered it a moral obligation for patients to understand the nature and risks of anesthesia techniques to be used on them prior surgery.

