### Methods: data collection, management, and analysis

#### Data collection

Data will be collected by the PI and trained research assistants using a pre-designed and pre-tested structured questionnaire after educating participants for the need and significancy of follow up. The data collection tool was designed in English (the official language in Uganda) with translation in local language for the illiterate. A content validity index of 78% from 15 pre-test participants was considered adequate. Parts A and B of the questionnaire on socio-demographic and grade and size of goiter will be filled and completed. Part C of the questionnaire will be filled with intraoperative events. Part D of the questionnaire will be filled post-operatively and during follow up.

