### Data management and analysis

Data will be coded, entered in Excel version 2016, and later exported to STATA 14.2. for analysis. The intention-to-treat model will be used to minimize bias as way of reflecting what happens in real clinical practice. The intention-to-treat population will be used for inference and will be defined as all eligible randomized patients recruited in this study. Analysis will be done per study objective. Socio-demographic and surgical factors will be summarized descriptively using summary measures as proportions, means, medians, and measures of variation such as standard deviations for means, interquartile range for medians. All analyses will be computed at 95% confidence intervals and regarding *p* < 0.5 as statistically significant.

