## Objective one

The occurrence of early post-operative complications of euthyroidectomy under the two arms (LA and GA) of the study will be measured by total occurrence of a particular complication divided by the total number of euthyroidectomy done under LA and GA, respectively. These will be expressed as percentages with 95% confidence interval and the difference in proportions will be compared using a two-sample Student’s *t*-test, assuming normal distribution and equal variance. The Shapiro–Wilk test will be used to assess for normalcy of distribution whereas Levene’s test will be used to assess for equality of variance.

For the pain scores, visual analogue scale will be stratified as no pain (0), mild (1–3) or moderate (4–6), and severe (7–10) and the difference in proportions will be compared using non-parametric Kruskal–Wallis rank sum test (H). The overall occurrence of adverse events in both groups will be summarized as proportions in accordance with Clavien Dindo classification [27].

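### Goiter grade and size, ASA class and age are recorded at baseline but no comparison adjusts for them: a valid analysis that may give up some precision on the pain and nausea scores

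*Protocol article*

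**What the plan says.** **Baseline data.** Under Independent variables: "Information will be captured on baseline characteristics such as sex, age, comorbidities, and ASA classification". Under Data collection: "Parts A and B of the questionnaire on socio-demographic and grade and size of goiter will be filled and completed".

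**Use of these data.** Under Data management and analysis: "Socio-demographic and surgical factors will be summarized descriptively". The Missing data section adds a comparison of baseline characteristics between groups for participants without end points. No section brings a baseline value into an estimate of the treatment effect.

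**Comparisons named.**
- Pain: "The mean pain scores will be compared at using" a Student's t-test, with a Kruskal–Wallis fallback (Primary outcome measures). Objective one also compares pain categories by Kruskal–Wallis.
- Nausea: a paired t-test, with the same fallback (Primary outcome measures).
- Graded complications: "The difference in proportions will be compared using Wilcoxon sum rank test" (Primary outcome measures).
- Complication percentages: "the difference in proportions will be compared using a two-sample" t-test (Objective one).
- Cost: t-test (Objective two).
- Satisfaction: Kruskal–Wallis (Objective three).

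**Randomization.** "Permuted balanced block randomization will be performed by the study supervisor", in a 1:1 ratio, with no patient factor named for stratification.

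**The concern.** Neither the design nor the analysis uses what is known about each patient before surgery. The article itself gives a reason to think that one of these values matters. Its exclusion criteria remove patients with factors said to affect the result of thyroidectomy independently, and grade 3 goiter heads that list. Grades 1 and 2 both stay in the trial, so some spread in goiter grade remains.

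The trial is small and aims to show equivalence, so interval width matters. If goiter grade or ASA class predicts pain or nausea, unadjusted tests leave explainable variation in the error term and the intervals are wider than they need be. If the covariates are not named in advance and an imbalance then appears, any adjustment would be chosen after seeing the data.

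**Working it through.** **Inputs from the protocol article**
- 26 per arm including 10% for loss to follow-up; complication-free 83% (LA) and 79% (GA); margin 33 points; power 80%; type 1 error 0.05 (Sample size estimation).
- 52 numbered envelopes (Randomization section). The abstract says 29 per arm, so both sizes are checked.
- The share of outcome variance explained by the covariates, R², is not given. It is an assumption here, from 0 to 30%.

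**1. The plan's own sample size**

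Equivalence of two proportions, each one-sided test at 0.05, unpooled variance, true difference of 4 points toward the margin:

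n = (0.83×0.17 + 0.79×0.21) × (1.645 + 0.842)² / (0.33 − 0.04)² = 0.307 × 6.18 / 0.0841 = 22.6, so 23 per arm.

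23 / 0.9 = 25.6, so 26. The stated figure reproduces on this reading; the article does not state the sidedness.

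**2. How often baseline imbalance arises at 26 per arm**
- Continuous factor: the SE of the standardized difference is √(2/26) = 0.277. P(|d| > 0.5) = P(|Z| > 1.80) = 7%; P(|d| > 0.3) = 28%.
- Binary factor: P(difference of 20 points or more), exact binomial, is 12.6% at 50% prevalence, 9.5% at 30% and 5.5% at 20%.

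**3. Does imbalance harm the unadjusted test?**

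In 10,000 simulated trials of 26 per arm with four prognostic covariates, the unadjusted test rejected a true null in 5.0%, 5.4% and 5.1% of trials at R² of 0, 10% and 30%. The level holds.

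**4. Precision from adjustment of a continuous score**

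Variance ratio, adjusted to unadjusted, with k covariates: (1 − R²)(2n − 3)/(2n − k − 3).

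For n = 26 and k = 2 the factor is 49/47 = 1.043:

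| R² | variance ratio | equivalent change in patients |
|---|---|---|
| 0 | 1.043 | −4% |
| 10% | 0.938 | +7% |
| 20% | 0.834 | +20% |
| 30% | 0.730 | +37% |

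Break-even R² = 1 − 47/49 = 4%.

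Other choices at n = 26:
- One covariate: ratio 0.92 at R² 10% and 0.72 at 30%; break-even about 2%.
- Four covariates: ratio 0.98 at R² 10% and 0.76 at 30%; break-even about 8%.

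At 29 per arm and k = 2 the factor is 55/53 = 1.038. The gain is again about 7% at R² 10% and about 38% at 30%.

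**5. The dichotomous outcome**

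Expected patients with any complication: 26×0.17 + 26×0.21 = 4.4 + 5.5 = 9.9. About 10 events cannot support a logistic model with several covariates. The table in step 4 does not apply to this outcome.

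**The case against.** The strongest reply is that comparing randomized arms without adjustment is correct, that adjusted analyses are commonly left to an analysis plan that is not shown, and that the precision gain rests on an R² found nowhere in the document. Validity stands in full. So does the point about R²: the gain could be small or slightly negative. The appeal to an unseen plan stands only in part. The article is not silent; it names a test for each outcome and gives the baseline factors a descriptive role. The suggestion therefore concerns a stated choice, although a later plan could add to it.

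The exclusion list also gives limited support. It shows that the authors treat advanced goiter grade as prognostic. It does not say so of grade 1 against grade 2, nor of ASA class, age or sex. Goiter grade is the best-supported covariate, but that remains an inference.

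A reader might infer that chance imbalance biases the result or inflates false positives. It does not: the unadjusted standard error already allows for it. Given a 0.5 SD imbalance, the difference test would reject in about 7.5% of trials at R² 10% and 12% at 30%. That condition occurs in only 7% of trials per factor, so it is not likely, and with zero imbalance the rate falls to 3.9% and 1.9%. These rates also belong to a test of difference, not to a false declaration of equivalence.

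A reader might also take the gain as 1/(1 − R²) − 1, that is 11% to 43% for R² of 10% to 30%. That ignores the degrees of freedom spent on the covariates.

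**Conclusion.** The point holds as one of efficiency. The baseline values are collected, every named comparison is unadjusted, and no stratification is stated. With two covariates and 26 per arm, adjusting the continuous scores is worth about 7% more patients at an assumed R² of 10% and about 37% at 30%. The cost is equivalent to about 4% of the patients if the covariates explain nothing. The conclusion is the same at 29 per arm.

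The document does not support calling the planned comparisons biased or invalid, nor adjusting for every listed covariate. It also does not support describing all comparisons as two-sample tests: nausea is assigned a paired t-test, which does not suit independent arms and is a separate error. The gain applies to the pain and nausea scores, not to the dichotomous outcome that set the sample size.

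**What to change.** In Primary outcome measures, make the main comparison of pain and nausea scores a linear model with arm, goiter grade and at most one further covariate named in advance, such as ASA class. Keep the unadjusted or rank-based two-group comparison as a sensitivity analysis, which matters because both scores are bounded. This also replaces the paired test for nausea. Align the pain analysis under Objective one with this choice.

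For the complication-free outcome, keep the unadjusted risk difference with its confidence interval as primary. If adjustment is wanted, use goiter grade alone and report a standardized risk difference.

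The cost is wording only: no new data and no more patients. The downside is the slight loss of precision if the chosen covariates are not prognostic.

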### Sample size estimation

Sample size estimation in this study assumes a null hypothesis that there is no difference in early post-operative outcomes for euthyroidectomy under LA versus GA (equivalence study). In a study that evaluated the measurement of acute post-operative outcomes amongst patients who undergo surgery, a patient acceptable symptom state, i.e., the value beyond which patients considered themselves well, was documented at 33% [28]. Based on a study at the Scott and White Memorial Hospital, in Texas, the proportion of patients who underwent euthyroidectomy under LA with no identifiable complication were 83% as opposed to 79% who underwent GA [16]. Therefore, assuming a statistical power of 80%, type 1 error of 0.05, and a threshold for equivalence in effect with a dichotomous outcome that LA is no better or worse than GA by a minimal clinically important difference of 33% in the primary outcome measures; the sample size estimation based on Cleveland Clinic sample size estimation in clinical research (https://riskcalc.org/samplesize/) [29] will be 26 for each arm (1:1 allocation), including additional 10% to cater for loss to follow-up.

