Previous studies comparing euthyroidectomy under LA versus GA have shown mixed findings with regard to the benefits and post-operative outcomes. Other than overcoming the need to book for intensive care space and an anesthesiologist [14], which most patients in low-income countries cannot afford in the case of thyroidectomy under GA [15], LA has been associated with less post-operative pain, costs, hospital stay duration, post-operative nausea, vomiting, throat discomfort, and voice changes [9, 16, 17]. According to research in Nigeria [13], India [8], and USA [16], complications such as hematoma, surgical site infection, and colloid occur in less than 4% of cases of thyroidectomy performed under LA. In a randomized controlled study in Germany [9], the occurrences of post-operative complications (pain, nausea, vomiting, throat discomfort, painful swallowing, voice change, and difficulty in breathing were less in the group of patients who underwent thyroidectomy under LA as compared with those under GA in contrast to the prospective study in Uganda [18]. According to the USA [16] and Ugandan [18] studies, GA is also more associated with persistent hypothyroidism although the Kenyan cross-sectional review showed no difference[11].

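### The ±33-point equivalence margin is taken from a level at which an individual patient feels well, and it tolerates true complications of up to 54% under LA against 21% under GA

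*Protocol article*

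**What the plan says.** All the relevant text is in one paragraph of the protocol article, under Sample size estimation.

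- Origin of the figure: "a patient acceptable symptom state, i.e., the value beyond which patients considered themselves well, was documented at 33" per cent, attributed to a study of acute post-operative outcomes.
- Use of the figure: the design adopts "a threshold for equivalence in effect with a dichotomous outcome", worded as "LA is no better or worse than GA by a minimal clinically important difference of 33% in the primary outcome measures".
- Planning rates, from an earlier study in Texas: "the proportion of patients who underwent euthyroidectomy under LA with no identifiable complication were 83" per cent, "as opposed to 79% who underwent GA".
- Error rates: "assuming a statistical power of 80" per cent and "type 1 error of 0.05". Whether the 0.05 is one- or two-sided is not stated.
- Result: 26 per arm with 1:1 allocation, including 10% for loss to follow-up. The abstract gives 29 per arm, so the total is 52 or 58 depending on the place read.

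Data management and analysis says that all analyses use 95% confidence intervals. No other section gives a reason for 33 points.

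**The concern.** The paragraph gives one number two meanings. It first describes a level on a symptom measure at which a patient regards himself or herself as well. It then calls the same number a minimal clinically important difference and applies it to a yes/no outcome compared between arms. A level is not a difference, and a threshold for one person's symptoms does not say how many more patients with complications would be acceptable under LA.

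Equivalence is in the title, the trial design and the sample size. The Study rationale says that the results could inform use of LA as a comparable alternative to GA where resources are limited. The margin alone decides what equivalent means. If it has no clinical basis, a correctly run equivalence test protects only against a difference that nobody has argued to be the largest acceptable one.

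**Working it through.** **Inputs.** From Sample size estimation: complication-free 0.83 (LA) and 0.79 (GA), margin 0.33, power 80%, type I error 0.05, loss 10%, 26 per arm. The 29 per arm comes from the abstract. Assumption: 0.05 is spent on each one-sided test, which corresponds to a 90% interval. A 95% interval is shown alongside.

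**1. Reproducing 26 per arm.** For equivalence of two proportions with unpooled variance,

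n = [pL(1−pL) + pG(1−pG)] × (z0.95 + z0.80)² / (margin − |d|)²

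- Variance term: 0.83×0.17 + 0.79×0.21 = 0.1411 + 0.1659 = 0.307.
- (1.645 + 0.842)² = 6.183.
- Margin less planned difference: 0.33 − 0.04 = 0.29, squared 0.0841.
- n = 0.307 × 6.183 / 0.0841 = 22.6, so 23.
- With 10% loss: 23/0.9 = 25.6, so 26.

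This is the stated figure. A variant with 0.025 per side and no true difference also gives 23, then 26. In both, 33% enters as an absolute difference in proportions.

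**2. True rates that the margin tolerates.**

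- Lower limit: 79 − 33 = 46% complication-free under LA.
- Complications at that limit: 54% against 21%, and 54/21 = 2.57.
- Upper limit: 79 + 33 = 112%. At the planning GA rate the largest possible true LA advantage is 100 − 79 = 21 points.

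**3. How often equivalence would be declared.** Exact enumeration of both binomials, GA at 79%, Wald interval wholly inside ±33 points:

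| True LA complication-free | Complications LA v GA | 26/arm, 90% CI | 26/arm, 95% CI | 29/arm, 90% CI |
|---|---|---|---|---|
| 83% (planned) | 17% v 21% | 79.6% | 69% | 86% |
| 64% (15 points worse) | 36% v 21% | 42% | 29% | 46% |
| 59% (20 points worse) | 41% v 21% | 27% | 17% | 29% |
| 58% (complications doubled) | 42% v 21% | 25% | 15% | 26% |
| 46% (at the margin) | 54% v 21% | 5% | 2% | 5% |

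**4. Which limit causes failure.** At 83% v 79%, 26 per arm and a 90% interval, the lower limit stays above −33 in 95.7% of trials. The upper limit stays below +33 in 83.9%, and both hold in 79.6%.

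**5. What an observed result must look like.** With 26 per arm and 5 complications under GA, the largest LA count that passes with a 90% interval is 8 (31% v 19%). The interval is then −31 to +8 points.

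**6. What the trial can resolve.** The 95% half-width at the planning rates is 1.96 × √(0.307/26) = 0.213, or 21 points. With 23 evaluable per arm it is 1.96 × √(0.307/23) = 0.226, or 23 points. Solving the formula in step 1 for the margin at 80% power gives 0.04 + √(0.307 × 6.183/n): 33 points at n = 23, 31 at n = 26 and 30 at n = 29.

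For scale, and purely as assumed margins, the same formula needs the following per arm after 10% loss: 84 for 20 points, 175 for 15 points and 587 for 10 points.

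**The case against.** The strongest reply is that the test is properly sized and controls its error. The arithmetic behind 26 is right. At the limit of 54% v 21% a false declaration occurs in about 5% of trials, the nominal level. All of this stands, but it shows only that the calculation is sound given the margin. It does not supply a reason for the margin.

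The cited source is not available here, so its 33% might rest on another scale or have a fuller rationale. That also stands as a limit. The point rests on the protocol's own description, which is of a level, and on the absence of any bridging argument.

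Three stronger readings are tempting and are not supported.

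- **That the test is in effect one-sided because 112% cannot be reached.** A true LA rate above 100% is impossible, but equivalence is judged on the confidence interval. Its upper limit can cross +33, and at the planning rates it is the more frequent cause of failure (step 4).
- **That a trial observing more than twice as many complications under LA would pass.** The 2.6-fold ratio describes true rates inside the margin. In the example in step 5 the largest observed ratio that passes is 8/5 = 1.6.
- **That hematoma or infection could rise from 4% to 37% and qualify.** The Introduction says that "complications such as hematoma, surgical site infection, and colloid occur in less than 4% of cases", but this refers to thyroidectomy under LA, so it cannot serve as the GA reference. The sample size is also built on a single complication-free rate, not on each complication.

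The 42% and 27% in step 3 depend on a 90% interval. At the 95% level given in the analysis section they fall to 29% and 17%.

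**Conclusion.** The point holds. The margin is an individual symptom level relabelled as a between-arm difference, and the sample size depends on it. At the planning GA rate it classes any true LA complication rate below 54% as equivalent to 21%.

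In practice, at 26 per arm, a true deficit of 15 to 20 points would be called equivalence in 27% to 42% of trials with a 90% interval, or 17% to 29% with a 95% interval. These figures assume the planning GA rate of 79%, Wald limits and 26 evaluable per arm. The documents do not show that a margin of 33 points could never be defended. They show that it has not been defended as a difference in complication-free proportions.

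**What to change.** In Sample size estimation:

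1. Remove 33% as the between-arm margin, or justify it explicitly as an acceptable absolute difference in complication-free proportions. State a clinically argued margin.
2. State that, at the planning rates, 52 to 58 patients give 80% power only for a margin of about 30 to 33 points.

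In the analysis and conclusions:

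3. Report the LA−GA risk difference with its confidence interval, name the interval level used for the equivalence decision, and say which differences the interval excludes.
4. Claim equivalence only if the whole interval lies inside the justified margin. Otherwise present the result as an estimate.

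The cost is protocol wording and a more modest claim. No extra patients or data are needed, provided the authors accept that the present size may not confirm a narrower margin.

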**Methods:**

This prospective equivalence randomized, single-blind controlled trial protocol will be conducted among eligible participants with grade 1–2 uncomplicated euthyroid goiters. The recruitment processes will start in October 2022 and end in April 2023. Consenting participants with an indication for thyroidectomy will be randomized into two arms of 29 participants in each arm during the Bulamu Health Care Organization surgical camps in Uganda.

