### Data monitoring committee and auditing for harms

#### Interim analysis

The Kampala International University Western Campus Research and Ethics Committee will form an interim committee that will audit this study and have access to results of interim analysis which will be performed when the 30th patient is recruited (58% of total sample size). The committee will independently recommend continuation, modification, or termination of the study in accordance with its ethical guidelines in relation to safety of human research participants.

Such circumstances warranting termination include unbearable adverse effects or in the unlikely event of achieving differences between study groups. Otherwise, comprehensive results would be published in the final stages of dissemination.

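### The abstract randomizes 58 patients but the methods use 52, and on the protocol's own inputs 52 with 10% loss gives about 75% power for equivalence (about 60% with 95% intervals), not 80%

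*Protocol article*

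**What the plan says.** All places are in the protocol article.

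- **Abstract, Methods:** consenting participants "will be randomized into two arms of 29 participants in each arm", which is 58 in total.
- **Sample size estimation:** the number "will be 26 for each arm (1:1 allocation), including additional 10% to cater for loss to follow-up", which is 52 in total. The inputs are given in the same section: "assuming a statistical power of 80%, type 1 error of 0.05"; a margin such that "LA is no better or worse than GA by a minimal clinically important difference of 33% in the primary outcome measures"; and proportions of patients "with no identifiable complication were 83% as opposed to 79% who underwent GA".
- **Randomization, blinding and allocation concealment and implementation:** "A set of 52 numbers will be generated beginning with a minimum of 1 and maximum of 52". These numbers label the envelopes.
- **Interim analysis:** the interim takes place "when the 30th patient is recruited (58% of total sample size").
- **Data management and analysis:** all analyses use 95% confidence intervals, and the intention-to-treat population is all eligible randomized patients.

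**The concern.** There are two problems.

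First, the number of patients to randomize is stated as 58 in one place and as 52, directly or by implication, in three others. Two totals lead to different envelope sets, different interim fractions and different power.

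Second, the trial is declared an equivalence trial with a margin in both directions, so both margins must be excluded for it to succeed. The 80% power claimed for 26 per arm, after allowing for loss, should be the probability of passing both tests. If it is lower, the trial has a larger chance than stated of ending without a conclusion even when the two techniques are as similar as assumed.

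**Working it through.** **1. Which total each section uses**

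- Abstract: 2 × 29 = 58.
- Sample size section: 2 × 26 = 52.
- Randomization list: 52.
- Interim: 30/52 = 57.7%, which rounds to the stated 58%; 30/58 = 51.7%. The interim fraction is therefore based on 52.

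Three sections agree on 52. Only the abstract differs.

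**2. Inputs for power**

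From the sample size section: LA 0.83, GA 0.79 (difference 0.04), margin ±0.33, power 80%, type 1 error 0.05, loss 10%. The section does not say whether 0.05 applies to each one-sided test. I use 0.05 per test (a 90% interval), then 0.025 per test (a 95% interval, as in the data analysis section).

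Sum of variances: 0.83 × 0.17 + 0.79 × 0.21 = 0.1411 + 0.1659 = 0.307.

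**3. Reproducing the protocol's 26**

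One-sided formula at the nearer margin: n = 0.307 × (1.645 + 0.842)² / (0.33 − 0.04)² = 22.6, so 23 evaluable per arm. With 10% loss, 23/0.9 = 25.6, so 26. This matches 26 including 10%, but it counts the risk of failing at one margin only.

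**4. Power with both margins tested**

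SE = √(0.307/n), and

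power = Φ((0.33 − 0.04)/SE − z) + Φ((0.33 + 0.04)/SE − z) − 1.

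Randomizing 26 per arm with 10% loss leaves 26 × 0.9 = 23.4, about 23 evaluable. At n = 23, SE = 0.1155.

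- z = 1.645: Φ(0.865) + Φ(1.558) − 1 = 0.807 + 0.940 − 1 = 0.747.
- z = 1.960: Φ(0.550) + Φ(1.243) − 1 = 0.709 + 0.893 − 1 = 0.602.

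The first term at z = 1.645 (80.7%) is the power that the one-sided formula delivers. The second margin takes off about six points.

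| Evaluable per arm | 90% CI, normal approx. | 90% CI, exact enumeration | 95% CI, normal approx. | 95% CI, exact enumeration |
|---|---|---|---|---|
| 23 (26 randomized, 10% lost) | 74.7% | 74.3% | 60.2% | 61.5% |
| 26 (29 randomized, 10% lost) | 80.8% | 79.6% | 68.7% | 69.2% |

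The exact columns enumerate both binomial outcomes and apply the Wald interval rule.

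**5. Sensitivity to the true difference**

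With a true difference of zero, 23 evaluable per arm and a 90% interval, power is 73.0% if both rates are 79%, 77.3% if both are 81%, and 81.8% if both are 83%.

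**6. What the numbers cannot show**

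- 26 arises in two ways: as 23/0.9 from the one-sided formula, or as the evaluable number for 80% joint power under the normal approximation (25 gives 78.9%, 26 gives 80.8%).
- 29 also arises in two ways: as 26/0.9 = 28.9, or with no allowance for loss from the one-sided formula at 2.5%, 0.307 × (1.960 + 0.842)² / 0.29² = 28.65.
- Exact enumeration gives 80.1% at 25 and 79.6% at 26, so 26 is not a unique threshold.
- The usual closed form for equivalence, which halves the type 2 error, gives 0.307 × (1.645 + 1.282)² / 0.29² = 31.3, so 32 evaluable, and 36 after loss.

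**The case against.** The best defence of 52 is that the three sections that drive the trial (target, envelopes, interim) agree with each other, so the abstract may simply be wrong. That stands. It follows that six patients would lack an envelope only if the abstract overrides the other three sections.

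A second defence is that a standard formula returns exactly 26 including 10%. That also stands as arithmetic. It does not rescue the 80%, because the formula leaves out one of the two tests that an equivalence claim needs.

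A reader might infer that 26 is the number before the allowance for loss, that 29 is the number after it, and that the sample size section is therefore wrong to say that loss is included. The match is tempting, but the documents do not support the inference. Both figures can be reached by other routes, the match to 26 depends on the normal approximation, and the online calculator that the section cites could not be run. The derivation of either figure cannot be told from the text.

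Third, the 75% is conditional. It assumes a true difference of 4 points, whereas the section also speaks of no difference. At zero difference with both rates at 83%, power at 52 randomized exceeds 80%. That stands as a qualification, but 83% in both arms is not the pair of rates that the protocol assumes.

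Finally, the protocol analyses all eligible randomized patients and imputes missing endpoints. Imputation keeps patients in the denominator but does not restore the information lost, so it qualifies the figure of 23 per arm without removing the shortfall.

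**Conclusion.** The contradiction between 58 and 52 is certain and needs no assumption.

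The power statement is wrong as written for a two-sided equivalence claim. At 52 randomized with 10% loss, power is about 75% with a 90% interval and about 60% with a 95% interval, against the stated 80%. These figures rest on the protocol's own rates of 83% and 79%, its margin of 33 points in both directions, and about 23 evaluable patients per arm. With a true difference of zero and common rates of 79% to 83%, the 90% interval figure is about 73% to 82%. The shortfall is thus about five points on the more favourable choice of interval and about twenty on the one that the analysis section names.

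No conclusion is drawn on how 26 or 29 was obtained.

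**What to change.** Use one total in the abstract, the sample size section, the randomization list and the interim section.

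- **Keep 52 (cheap option).** Correct the abstract to 26 per arm, and restate the equivalence power as about 75% (90% interval) or about 60% (95% interval). The list and the interim fraction stay as they are. The cost is editing text.
- **Use 58, if that is the real target.** State 29 randomized and about 26 evaluable per arm after 10% loss, with power of about 80% (90% interval) or about 69% (95% interval). Extend the list and the envelopes to 58, and restate the interim as 30/58 = 52%. The cost is six more patients than the current list covers, within 4–5 camps and a recruitment period that ends in April 2023.

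In either case, name the interval, 90% or 95%, on which equivalence will be judged, and make the stated power refer to it.
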